## Discussion

The study helps to fill existing knowledge gaps, and we have summarized the significance and contribution to research as follows:Most research concerning the oral status of older adults is based on older adults being able to participate in the data collection at dental care clinics [63]. The digital platform will provide a foundation for a register of the oral status of older adults in home settings, including older adults who are unable to participate in dental care clinics. This will support understanding of oral status in home settings of older adults, and of how to design and plan interventions to support healthy ageing.Older adults are included in every part of this project, including as co-authors. This emphasizes the participatory aspect of healthy ageing, and also the notion of conducting research *with*, as a complement to *on* human beings [64]. Stakeholders within municipal organizations are also included as partners, emphasizing the importance of bridging theoretical and practical understanding when developing research. Co-creating knowledge within social practices of working life, might contribute to further understanding lifelong learning and healthy ageing.The way in which health care planning is conducted in home settings is crucial for conducting person-centred care [2]. To our understanding, there is no available conceptual model involving older adults as well as dental and healthcare professionals based on a theory of shared decision-making. Within the project, this will be explored and further developed.Having a shared tool during health care planning in home settings is important for health care planning and decision-making [32]. There are, to our knowledge, no interorganizational digital platforms for older adults that bridge dental and municipal healthcare and enable long-term, integrated care. Evaluating the interprofessional shared digital platform and the activities within the work-model will further contribute to theory and practice by adding knowledge in these domains.Healthcare and dental care need to be further integrated [4] and poor oral health is often preventable, chronic and socially derived [20]. The use of the interorganizational digital platform can probably be extended to other areas besides home settings. This could further enable diverse interorganizational projects and innovations, which might contribute to research closing the gap between the separate knowledge domains of healthcare and dental care.The coordination aspects of the interorganizational project are major [9]. Assisted by the digital platform, coordination might be further developed with artificial intelligence (AI). As such, the project may also further contribute to research within artificial intelligence areas since there is a need for bridging the gap between research within the domains of AI design and healthcare [65].A prerequisite for healthy ageing is change and learning [49]. How learning and change are defined, discussed, and considered is therefore crucial. For example, implementing a new work- model and a digital platform requires change and learning. However, there is uncertainty about what kinds of work-life experiences generate what kinds of knowledge and actions [66]. Using theories within change and learning when analysing outcomes within this project might contribute to identifying and learning new knowledge [67]. Also, iteratively co-developing the work-model and digital platform is expected to bridge research and practice for the promotion of healthy ageing.

The results of this study can be applied in clinical practice immediately. If the interorganizational model, supported by the digital platform, has positive outcomes, the model and digital platform can readily be implemented in home settings in Sweden, and probably also internationally. Furthermore, the results of the study can guide the development of person-centred care and guide future change and learning approaches within interorganizational collaborative domains to facilitate healthy ageing.

## Trial status

This study is registered at Clinical Trials.gov—registration date 13 March 2024. This is the first study protocol, dated the 25th of November 2024. Recruitment and randomization of participants are planned to start in September 2025. The data collection plan is to be completed in September 2026.

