### Data analysis

Descriptive data will be presented using the mean and standard deviation (SD) or median and interquartile range for numeric variables, as appropriate. Categorical variables will be presented in numbers and percentages. The efficacy evaluation will be conducted according to intention-to-treat, including randomized subjects analysed by randomized treatment. Missing data will be imputed using multiple imputation. Drop-outs will be summarized descriptively by the treatment group with at breakdown of reasons for withdrawal.

Statistical analyses will be performed with appropriate methods for cluster RCTs using mixed effects models with DH as a random effect to account for intra-cluster correlations. Numeric variables will be adjusted for baseline values, if applicable. All questionnaire scales will be treated as numeric in this regard. Results will be presented using the mean difference between groups with 95% confidence intervals. The primary endpoints (change in ROAG and GOHAI from baseline to 12-month follow-up) will be tested at significance level *α* = 2.5%, a two-sided test, retaining the type I error rate of the primary endpoints at the 5% level. All other tests will be two-sided and conducted at the 5% significance level. No interim analyses will be conducted.

A total of 32 DH (16 per group) and 480 older adults (240 per group) will be included to demonstrate a clinically meaningful difference of 1 unit in ROAG at 80% power, adjusted for baseline values. The following assumptions were made: SD of change scores from baseline values = 3 since the older adults as a group are heterogeneous [45]. Weak to moderate correlation between baseline values and change scores = 0.3, m = 15 older adults per DH, a weak intraclass correlation coefficient within clusters = 0.05, significance level *α* = 0.025, two-sided test, and 25% drop-out [59]. A weak intraclass correlation coefficient is expected since DH is a licensed profession in Sweden, and ROAG is a validated instrument which shows little intraclass difference over time in nursing care [62]. A blinded evaluation of the SD, correlation, and intraclass coefficient will be conducted when 6-month follow-up data has been retrieved for 50% of the planned study participants, with a possibility for sample size adaption if judged necessary. Sample size calculations were conducted using SAS/STAT® Software, Version 9.4 of the SAS System for Windows (SAS Institute Inc. Cary, NC, USA).

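### The stated calendar, September 2025 to September 2026, does not accommodate 12-month primary endpoints for 480 participants or any sample-size increase after the blinded review

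*Protocol article*

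**What the plan says.** Trial status in the protocol article gives two dates: "Recruitment and randomization of participants are planned to start in September 2025. The data collection plan is to be completed in September 2026". No other section gives an accrual period, a date for last enrolment or a later end.

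The Data analysis section defines the primary endpoints as "change in ROAG and GOHAI from baseline to 12-month follow-up", and the outcome list under Phase VI agrees. The 12 months run from each participant's own baseline.

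On size, Data analysis states: "A total of 32 DH (16 per group) and 480 older adults (240 per group) will be included". The same section plans a blinded look at the SD, the correlation and the intraclass coefficient. This "will be conducted when 6-month follow-up data has been retrieved for 50% of the planned study participants". The numbers may then be changed, since the look comes "with a possibility for sample size adaption if judged necessary".

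**The concern.** The start and end dates are about one year apart, and the primary outcome takes one year to observe. Almost nothing is left for enrolment. The calendar also has no room for what may follow the blinded review, because participants added at that point need a further 12 months.

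Two things are at stake. If the dates are followed as written, later enrollees have no primary outcome by the stated end. And the article's only stated check on its SD, correlation and intraclass assumptions could lead to a larger sample that the calendar cannot follow up.

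**Working it through.** **Inputs from the article.** Start September 2025 and end September 2026 (Trial status). Primary follow-up 12 months, 480 older adults, 32 dental hygienists, and review at 6-month data on 50% (Data analysis). Six coordinators collecting consent and data (Phase VI). The planned 480 is taken as given, because this point does not depend on how it was derived.

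**Step 1: enrolment window.** The widest reading of the two months is 1 September 2025 to 30 September 2026, which is 394 days. Latest enrolment with a 12-month visit = end date − 12 months = 30 September 2025. Window = 394 − 365 = 29 days after the first possible day. On the narrowest reading (30 September 2025 to 1 September 2026) the span is 336 days, and no 12-month visit fits at all.

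**Step 2: workload in that window.** 480 / 30 calendar days = 16 baselines per day. If the six coordinators take all of them, 480 / 6 = 80 each. Assuming 22 working days and no start-up time, 80 / 22 ≈ 3.6 per coordinator per working day. Randomisation of the 32 hygienists must fit in the same month.

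**Step 3: earliest review.** Trigger = 0.5 × 480 = 240 participants with 6-month data. Even if all 240 were enrolled on 1 September 2025, the review could not come before 1 March 2026. The last enrolment date compatible with the stated end is 30 September 2025, five months before that. A participant added on 1 March 2026 reaches 12 months on 1 March 2027, five months after the stated end.

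**Step 4: what a realistic accrual implies.** The article states no accrual period, so assume uniform accrual over A months from the start of September 2025. Then:

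- last planned 12-month visit at month A + 12;
- review at month A/2 + 6;
- 12-month visit of someone added at the review at month A/2 + 18.

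| A (months, assumed) | Review | Last planned 12-month visit | 12-month visit if added at review |
|---|---|---|---|
| 3 | month 7.5 (April 2026) | month 15 (December 2026) | month 19.5 (April 2027) |
| 6 | month 9 (June 2026) | month 18 (March 2027) | month 21 (June 2027) |
| 12 | month 12 (September 2026) | month 24 (September 2027) | month 24 (September 2027) |

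The review falls before accrual closes only if A/2 + 6 < A, that is, A > 12 months. With shorter accrual, enrolment has already ended when the review takes place and would have to be reopened.

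**The case against.** The strongest defence is that Trial status is a forecast. It gives months, not days, and ties no database lock or analysis to September 2026. If accrual ran slowly, the natural response would be to move the end date. The Project organization section provides for protocol changes and a registry update. The review offers only a possibility of adaptation, and a provisional end date for the planned 480 need not include a contingent extension. At 3.6 baselines per coordinator per working day, a one-month enrolment is tight but not arithmetically impossible.

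Much of this stands, and it rules out several stronger readings that a reader might infer:

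- *That there is no enrolment period at all.* The widest reading leaves up to 29 days.
- *That the primary analysis would rest largely on imputation.* With uniform enrolment over 2, 3 or 6 months, (A − 1)/A = 50%, 67% or 83% would lack a 12-month visit at the end of September 2026. That becomes missing data only if collection stops on that date regardless of who is still in follow-up, and the article does not say so.
- *That all test teams must also be trained within September 2025.* The two-day course comes before the intervention assessments, but the text does not place it before the baseline measures that start the 12-month clock.
- *That the registry date is wrong.* The article shows only the date of registration.
- *That the review can never be acted on.* It cannot within the stated dates; an extension would make it possible.

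The defence does not remove the mismatch. These are the only dates given, and they conflict with the endpoint definition. If the trial is expected to run longer, the end date is wrong as stated. If the sample may grow, the article needs to say how those added will be followed.

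**Conclusion.** The point holds as an inconsistency between the stated calendar on one side and the 12-month primary endpoints and blinded review on the other. At most 29 days are available for enrolment, and anyone enrolled from October 2025 falls outside the stated end. A sample-size increase comes at least five months too late to be followed for 12 months within the stated dates.

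These results take the completion of data collection in its natural sense, as the last follow-up, and assume visits at exactly 6 and 12 months, since the article gives no visit windows. An allowance for early visits would widen the window only by its own length. The accrual lengths in the table are assumptions; the 29-day limit and the March 2026 and March 2027 dates do not depend on them.

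No endpoint, test or model has to change. The dates should be corrected before recruitment opens, because followed literally they defeat the primary endpoint for later enrollees.

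**What to change.** 1. State the planned accrual period.
2. Replace the fixed end date with a rule such as: *data collection ends 12 months after the last participant's baseline, including any participants added after the blinded review*. An indicative date can be given alongside it.
3. Keep the blinded review. A calendar problem is no reason to drop it. State whether enrolment stays open or is reopened after it, with full 12-month follow-up for those added. Under uniform accrual, staying open requires more than 12 months of accrual, and data collection then ends after about September 2027. With shorter accrual, enrolment must be reopened. An end in spring 2027 for added participants is realistic only if half the sample enrols almost at once.
4. Check that the completion date in the trial registry agrees with the revised text.

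The cost is a text change and a longer calendar, with the staffing that goes with it. The 12-month endpoints already imply most of that extension; the rest arises only if the review leads to a larger sample.

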### Project organization

This project is conducted in collaboration with the Center of Gerodontology and the Dental Public Health Care organization Region Västra Götaland; University West, in Trollhättan; University of Gothenburg; Chalmers University of Technology (CUT) – Centre for Healthcare Architecture; in joint discussion with municipal care organizations, older adults and their significant others. In case of changes, we will notify sponsors and funders, and a copy of the revised protocol will be sent to the Investigator Site File. Any deviations from the Protocol will be fully documented using a breach report form. We will also update the protocol in the clinical trial registry.

## Data Availability

Participants within the project have given permission for their data to be used. In agreement with GDPR, the data are to be used only for the purpose of these studies.
